### Outcome measures

The main outcome measure is the occurrence or not of lapse and/or relapse episode(s) during the three months after the intervention (follow-up assessment). The treatment status (any medication intake and other form of therapeutic intervention) at the follow-up assessment is also considered in comparison to the baseline status.

Secondary outcome measures include changes in the automatic cognitive biases as assessed with the VPT and AAT at post-intervention and follow-up assessment sessions. At the follow-up assessment, VPT and AAT present the same stimuli of the post-intervention session, to check for the duration of the training effects.

Generalisation effects of the two CBM modules to other measures are assessed at post-intervention with the BIAT [20-22]. Other secondary outcome measures (assessed at each measurement point) also include other substance abuse (CORE questionnaire), alcohol-related problems (AUDIT), craving (OCDS), anxiety (STAI-Y), depression symptoms (BDI-II) and motivation to treatment (MAC2-A; measured at pre- and post-intervention only).

Intervention credibility and expectancies are also assessed with the Credibility/Expectancy Questionnaire [50] to evaluate participants’ general experience with the study.

### Data analysis

Complete analyses will be conducted in agreement with Intention-To-Treat principle [26]. Missing data points will be handled with multiple imputation.

To answer to the main research question, a multiple logistic regression will be used to estimate how much the main and combined exposure to the two CBM modules affects the occurrence of lapse and/or relapse episodes at the three-month follow-up assessment.

The secondary research question, whether participants approach and attentional biases do change after the CBM intervention, is addressed via a 3×2×3 repeated-measures mixed ANOVA with the AAT and VPT scores as dependent variables, time (baseline, post-intervention and follow-up) as repeated measures within-subject factor, drink type (alcoholic and non-alcoholic) or attentional process (engagement and disengagement) as within-subject factor, and CBM condition (re-training or placebo) as between-subject factor. The same analysis applies to the continuous secondary outcome measures administered at each time point.

The third research question of the present study is framed within a ‘what works best for whom?’ approach [8] and explores the moderating and mediating roles of individual differences variables on the clinical outcome by means of a moderated mediation analysis [51]. More precisely, baseline strength of the cognitive biases and interference control capacity (Stroop task), as well as age, gender and previous detoxifications, are hypothesised to moderate the change in cognitive bias after the CBM intervention, which is further hypothesised to eventually mediate the change in the clinical outcome variable (see Eberl *et al*. [19]).

Finally, participants’ motivation to change (MAC2-A) at pre- and post-intervention will be compared via a paired t-test. Via a repeated-measures ANOVAs we will explore whether change in participants’ motivation to carry on with the training after the brief MS interviews affects attrition and training outcome.

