### The present study: aims and hypotheses

The aim of the current study is to investigate the effectiveness of combining computerised alcohol attentional bias and approach bias CBM trainings in adult alcohol-dependent outpatients alongside a motivational approach to sustain the training progression. The primary goal is testing the main and added effects of the CBM interventions on remission progress from alcohol addiction immediately after the intervention and three months later, with changes in the number of lapse or relapse episodes as primary outcome measure. It is expected that, for each of the two CBM training modules, participants in the active training condition will show a lower percentage of lapse or relapse than participants in the placebo condition [16-19].

Secondary outcome measures include changes in alcohol-related cognitive biases following the combined CBM intervention. Interaction effects between the CBM modules are explored, as well as the additive effect of exposure to the combination of the two CBM trainings. It is expected that each CBM paradigm will decrease or reverse the targeted bias and that these changes might mediate the effects on the clinical outcome (see Eberl *et al*. [19]). Further, it is expected that joint exposure to both active CBM re-trainings will have a greater beneficial effect than each of the active CBM re-trainings separately.

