## Methods/Design

### Trial design

The present study is a phase II, double-blind, parallel group RCT. Following the design of previous CBM studies [18,19], participants complete 11 sessions of either the active or placebo version of both attentional and approach bias training modules. The experimental intervention has a 2×2 factorial design, which combines the active and placebo training modules into four experimental conditions: one double active training experimental condition, two experimental groups receiving one active training and one placebo training and one double placebo training control group. According to the experimental design, the probability of receiving at least one active CBM intervention reaches 75%. The placebo version of each training module consists of a continuous assessment, in which half of the trials train the cognitive biases away towards alcohol and the other half towards soda (active placebo). The manipulation of the stimulus-response contingency in each task allows for a controlled and clean comparison between experimental conditions while retaining the same tasks, stimuli and instructions. Also, Wiers *et al*. [18] found no differences between continuous assessment and no-training placebo conditions, which suggested that either type of placebo could be used.

Participants complete a total of 14 sessions: two baseline assessment sessions, 11 training sessions, one post-intervention assessment session and one three-month follow-up assessment session. Participants complete the training sessions with a between-session time interval of a maximum of five days. The post-intervention assessment takes place between the 10th and 11th training session during a ‘masked’ session (participants do not know they are completing the post-intervention evaluation). That is to avoid possible negative feelings related to the final ‘evaluation’ of the intervention and minimise self-presentation biases and/or preparatory strategies.

Participant flowchart as per Consolidated Standards of Reporting Trials (CONSORT) statement [27] is presented in Figure 1. The study was approved by the Ethics Committee of the School of Psychology of the University of Padova (March 2013; Protocol number: 1242) and registered at Current Control Trials (identifier: ISRCTN01005959).

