The third strength of the study lies in the adoption of a factorial design, which allows the detection of the main but also the incremental effects of combining two CBM interventions. Unfortunately, the main pitfall covers the lack of published results on the combination of different CBM paradigms, which did not permit the running of a proper *a priori* power analysis to set out the optimal sample size, as the effect of simultaneously targeting two cognitive biases at once is still unknown. The same applies to possible interaction effects between the two re-trainings, since as yet no published studies have tested, for instance, the effect of an approach bias re-training over the attentional bias or vice versa. These shortages could be considered as a drawback of the study in terms of power; however, they are also part of the main strengths, since the exploration of any interaction and/or additive effect of multiple CBM interventions is a key objective of the present study, and potentially fruitful for CBM research and clinical applications. Furthermore, a sensitivity power analysis for a multiple logistic regression makes it possible to at least have an ideal projection of the minimal detectable effect for the main effects of the two training modules. The identified values can then be used as a guideline when carrying out the data analysis of the present RCT and check for the actual sensitivity of the test in detecting the sought effect.

Last but not least, the RCT design includes the assessment of the effects of the CBM modules in the long run by measuring participants’ cognitive biases in a follow-up session. So far, only a few studies have investigated the long-term effects of CBM on cognitive biases, particularly for attentional bias [55]. Given the potential of CBM, more extended evaluations of training effects and of the relation between (long-lasting) cognitive bias change and primary outcome have been called for [55]. In summary, the present longitudinal assessment of attention and approach bias in alcohol outpatients can be valuable for both assessing its application in an important patient category and gaining deeper understanding of the working mechanisms of CBM.

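### The secondary ANOVA is labelled 3×2×3 but its factors give 3×2×2, and its single CBM factor has no term for the module interaction or for one module's effect on the other bias

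*Protocol article*

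**What the plan says.** All references are to the protocol article.

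- **Data analysis** specifies a "3×2×3 repeated-measures mixed ANOVA with the AAT and VPT scores as dependent variables". Its first factor is time, at the three assessments. The second has two levels and depends on the task: "drink type (alcoholic and non-alcoholic) or attentional process (engagement and disengagement) as within-subject factor". Only one term distinguishes the randomised groups, and it too has two levels: "CBM condition (re-training or placebo) as between-subject factor". The next sentence gives the same analysis to the continuous secondary outcomes collected at every time point. By Table 1 and Outcome measures, those are the alcohol-problem, substance-use, craving, anxiety and depression questionnaires.
- **Trial design**: "The experimental intervention has a 2×2 factorial design". It yields four arms: both modules active, each module active alone, and both placebo. Sample size plans 30 participants per arm.
- **The present study: aims and hypotheses** says, in the paragraph on the bias outcomes: "Interaction effects between the CBM modules are explored, as well as the additive effect of exposure to the combination of the two CBM trainings". It expects each training to shift its own targeted bias, and joint active training to do better than either training alone.
- **Discussion** calls exploring interaction or additive effects a key objective. It mentions "the effect of an approach bias re-training over the attentional bias or vice versa" as something that published studies have not yet tested.

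**The concern.** There are three defects.

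1. The dimension label disagrees with the factor list in the same sentence, so an analyst cannot tell how many levels the between-subject factor is meant to have.
2. The randomised design has two crossed between-subject factors, and the model has one. The comparison of joint with single training, and the interaction, are stated aims for these outcomes and have no corresponding term.
3. When the model is carried over to the questionnaires, no training targets the outcome in the way that approach training targets the approach bias. It is then unclear which module the CBM factor refers to, and one of the within-subject factors is absent.

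At stake is whether a stated exploratory aim can be answered from the plan as written, and whether the coding of the CBM factor for the questionnaires is settled before the data are seen.

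**Working it through.** **Step 1: the label.** Levels as listed in Data analysis:

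- time: 3
- drink type (AAT) or attentional process (VPT): 2
- CBM condition: 2 (re-training, placebo)

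Product of the listed factors: 3 × 2 × 2 = 12 cells. Product of the label: 3 × 2 × 3 = 18 cells. The label is not reproduced. The four randomised arms would give 3 × 2 × 4 = 24 cells, the same as two crossed module factors, 3 × 2 × 2 × 2 = 24. None of these is 18.

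**Step 2: which between-subject contrasts each coding can estimate.** Order the arms as (approach, attentional) = (placebo, placebo), (placebo, active), (active, placebo), (active, active). The three factorial contrasts are:

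- approach module: (−1, −1, +1, +1)
- attentional module: (−1, +1, −1, +1)
- interaction: (+1, −1, −1, +1)

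A coding can estimate a contrast only if that contrast is a linear combination of the coding's columns, including the constant.

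| Between-subject coding | df | Approach | Attentional | Interaction |
|---|---|---|---|---|
| Approach module only | 1 | yes | no | no |
| Attentional module only | 1 | no | yes | no |
| Any active versus double placebo | 1 | no | no | no |
| Three levels: 0, 1 or 2 active modules | 2 | no | no | yes |
| Two crossed module factors | 3 | yes | yes | yes |

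The three-level coding would fit the label, but it contradicts the two levels named in "CBM condition (re-training or placebo) as between-subject factor". It also merges the two single-active arms, so it cannot give each module's effect separately.

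**Step 3: joint versus single training under the per-module reading.** For the AAT score with the approach module as the only CBM factor, arms (active, placebo) and (active, active) form one group of 30 + 30 = 60. Joint training versus approach training alone is the contrast (0, 0, −1, +1). It lies wholly inside that group, so the model cannot estimate it. The same holds for the VPT score with the roles of the modules exchanged.

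**Step 4: the questionnaires.** Two of the four arms have one active and one placebo module: 2 × 30 = 60 of 120 participants, or 50%. For a craving or anxiety score there is no own module to decide whether these 60 count as re-training or placebo. Nor do these scores have a drink type or an attentional process, so the second within-subject factor cannot be formed.

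**Step 5: precision of the added terms.** Take 30 per arm, no attrition and a between-person standard deviation σ. The standard error of a module main effect is σ√(1/60 + 1/60) = 0.183σ. For the interaction as a difference of differences it is σ√(4/30) = 0.365σ, twice as large. Crossing the factors costs 2 of the between-subject error degrees of freedom: 120 − 2 = 118 becomes 120 − 4 = 116.

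**The case against.** The strongest defence is that the document consistently defines active and placebo per module. It does so in the aims, in the descriptions of both trainings, in the count of two independent variables under Sample size, and in the sensitivity power analysis run separately for each module. On that reading the CBM factor for the AAT is approach training and for the VPT is attentional training. Each comparison is 60 versus 60, and in a balanced factorial leaving out the other module does not bias it. The question that Data analysis assigns to this ANOVA, whether the biases change after training, is then answered. This part of the defence stands.

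It rules out two stronger inferences. A reader might infer that the plan cannot test either module on the biases; per module, it can. A reader might also infer that condition means any active training against double placebo (90 versus 30), so that participants untrained on the measured bias dilute its effect and power falls. No section defines condition that way, and the document gives no power for the bias outcomes from which a loss could be calculated.

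Two further points also stand. The interaction is described as exploratory, and the primary logistic regression already covers both modules and their joint exposure. The Discussion remark on the effect of one training on the other bias describes a gap in the literature, not a hypothesis of this trial.

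It can also be said that a condensed article leaves full model terms to an analysis plan. That does not rescue the sentence. The article does state the model, its label contradicts its own factors, and the stated factors do not match the randomised design or the stated aims.

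**Conclusion.** The point holds in limited form. The label is wrong: 3×2×3 (18 cells) against listed factors of 3×2×2 (12 cells). With one two-level CBM factor, the model tests each module on its own targeted bias. It has no term for the interaction or combined effect that the aims plan to explore, nor for the effect of one module on the other bias. For the continuous questionnaires the instruction cannot be carried out as written: the CBM factor is undefined for half the participants and one within-subject factor does not exist.

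This rests on the four-arm design with 30 per arm and on reading active and placebo per module, which the rest of the document supports. The consequence is confined to secondary analyses. The primary outcome, its logistic regression, the randomisation and the sample size are not touched. No loss of power for the targeted-bias effects is claimed.

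**What to change.** - **Bias scores:** replace the label and the single CBM factor with time × drink type (AAT) or attentional process (VPT) × attentional CBM (active, placebo) × approach CBM (active, placebo), i.e. 3×2×2×2. Name the own-module × time effect as the main contrast. List the module × module (× time) and other-module effects as exploratory, which fits the aims and the doubled standard error of the interaction.
- **Continuous questionnaires given at all three time points:** state a separate model, time × attentional CBM × approach CBM, i.e. 3×2×2, without the drink-type or process factor.

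The cost is analysis-plan wording and two between-subject degrees of freedom. No change to data collection, recruitment or the primary analysis is needed. Trial status reports recruitment as still active, so the wording can be settled before analysis.

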### Sample size

The sample size is limited to 120 recruited participants due to constraints in the ratio between the number of potential participants fully meeting the eligibility criteria and available to participate in the study, out of the total number of alcohol-dependent outpatients currently in charge in the public service at the time of recruitment (3:10). Therefore, a realistic estimate of 120 participants (n = 30 per experimental condition) was considered achievable for a phase II RCT study, and further supported by a minimum number of cases identification analysis.

An operational guideline to identify the minimum number of cases to include in the study has been suggested by the Peduzzi *et al*. [52]. For *k* independent variables and *p* as the smallest of the proportions of negative or positive cases in the population, then the minimum number of participants is 10*k/p. Based on three previous CBM studies with alcohol dependent clinical populations, the average proportions of occurrence or absence of relapse event(s) at follow-up are about 0.53 and 0.47 after an approach bias or control re-training, respectively [18,19]; and about 0.40 and 0.28 after an attentional bias or control re-training, respectively [17]. The proportions were computed out of the total number of enrolled participants.

By taking the minimum among the four proportion values and setting *k* = 2 (two independent variables: attentional bias CBM re-training or placebo and approach bias CBM re-training or placebo), the minimum number of cases to be included in the present study is 10*2/0.28 ≅ 71. According to this approach, the proposed sample size is more than adequate to answer to the primary research question of the present study and should also allow for high attrition rates. It is worth noting that Wiers *et al*. [18] and Eberl *et al*. [19] had a one-year follow-up period, whereas Schoenmakers *et al*. [17] had a three-month follow-up period. The different follow-up timing allows only a partial comparison of the above-mentioned proportions. If similar proportions at one-year of follow-up were also observed in Schoenmakers *et al*. [17] then the minimum number of cases would decrease to 10*2/0.47 ≅ 43.

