## Discussion

The present paper describes the design of a double-blind RCT protocol to test the effectiveness of a computerised CBM intervention that targets alcohol-related maladaptive impulsive responses, which combines the attentional bias re-training and approach bias re-training in a 2×2 factorial design with the inclusion of motivational elements in each re-training session.

To the best of our knowledge, this is the first study to investigate the implementation of a combined CBM intervention alongside a targeted motivational intervention before each CBM session to sustain the training process in a clinical sample of outpatients. On a conceptual and clinical level, the combination of CBM with motivational elements specifically related to the contingent training context follows the dual-process account of addiction disorders, in which both the initial impulsive reactions to alcohol cues and the later in time, more reflective and deliberate processes can be targeted in intervention to bolster top-down control processes over impulses [8]. Weakening automatic appetitive processes by providing an alternative response option (training towards non-alcoholic stimuli) and simultaneously stressing the motivation (positive incentives) for more reflective and goal-directed behaviour is a double-pronged approach; both automatic and reflective processes are targeted. Furthermore, the motivation enhancement approach of the interview serves the purpose of levering participants’ commitment to and engagement in the training, which may well be perceived as monotonous and boring after a few sessions due to the inherent repetitiveness of the tasks.

One could argue that the MS should also have been experimentally manipulated to double-check its actual effects. Although that could have been experimentally optimal, it was not the main objective of the study. The leading focus was on the effects of the combination of two CBM interventions alongside the introduction of motivational elements. The MS was in fact conceived as a tool to optimise potential treatment effects of the CBM modules and to increase the acceptability and credibility of the CBM interventions, thus reducing attrition rates and improving the compliance to the training by subsuming the incentive value of long-term goal states [7,8].

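### Motivation to treatment (MAC2-A) is listed as a secondary outcome, but the only analysis named for it is a pre-post paired t-test with no condition factor

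*Protocol article*

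**What the plan says.** All places are in the protocol article.

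- **Outcome measures** names the questionnaire among the other secondary outcomes, with its own exception on timing: "motivation to treatment (MAC2-A; measured at pre- and post-intervention only".
- **Table 1** agrees on the timing (baseline and post-intervention, no follow-up). It puts MAC2-A in a separate row for motivation to treatment, not in the row for secondary outcome measures.
- **Data analysis** gives the bias scores a mixed ANOVA with "time (baseline, post-intervention and follow-up) as repeated measures within-subject factor" and "CBM condition (re-training or placebo) as between-subject factor". It then extends the model: "The same analysis applies to the continuous secondary outcome measures administered at each time point".
- **Data analysis**, closing paragraph, gives MAC2-A its own test: "motivation to change (MAC2-A) at pre- and post-intervention will be compared via a paired t-test". No condition factor is mentioned.
- The sentence after that plans repeated-measures ANOVAs on whether "change in participants’ motivation to carry on with the training after the brief MS interviews affects attrition and training outcome". This is the motivation-to-training measure, which Table 1 lists separately and schedules during the training sessions.

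**The concern.** The trial randomises two training modules in a 2×2 factorial. For a listed secondary outcome one expects a comparison between active and placebo for each module. Followed as written, the plan gives MAC2-A no such comparison: the model with condition in it does not reach MAC2-A, and the test that does reach it has no condition in it.

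The motivational support interview opens every training session in all arms, and all participants continue usual treatment. A pre-post change therefore combines passage of time, regression to the mean, usual care, motivational support and whatever the modules do. A significant result could be read as evidence for the training or for the support, and a null result as evidence against them. None of these readings would be justified.

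**Working it through.** The plan states no figure for MAC2-A, so there is none to reproduce. The check is first a reading of the text and then an illustration of what each test responds to.

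**1. Which analysis reaches MAC2-A?**

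| Analysis in the plan | Contains condition? | Covers MAC2-A? |
|---|---|---|
| Mixed ANOVA, three time levels | Yes | No: limited to measures taken at each time point, and MAC2-A has two of the three |
| Paired t-test, pre v post | No | Yes |
| Repeated-measures ANOVAs on motivation to train | Not stated | No: a different measure, examined for its effect on attrition and training outcome |

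No sentence compares MAC2-A between randomised conditions.

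**2. What each contrast estimates.** Let *c* be the mean change shared by all arms (time, regression to the mean, usual care, motivational support). Let *a* and *b* be the effects of the two modules on the change, taken as additive. With equal cells:

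- Mean change over all participants = *c* + *a*/2 + *b*/2.
- Active minus placebo for the first module = *a*.

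The pre-post mean cannot separate *a* or *b* from *c*. Motivational support is one component of *c*. Since no arm goes without it, no contrast in the trial isolates it. The Discussion accepts this: "One could argue that the MS should also have been experimentally manipulated to double-check its actual effects".

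If the t-test were instead run within each arm, the four tests would estimate *c*, *c*+*a*, *c*+*b* and *c*+*a*+*b*. Comparing their p-values is still not a test of *a* or *b*.

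**3. Illustration.** Inputs:

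- n = 120 with 30 per cell, from Sample size ("a realistic estimate of 120 participants (n = 30 per experimental condition"), hence 60 v 60 per module.
- Two-sided 5% tests and full follow-up.
- SD of change = 1. This is an assumption, as the document gives none. Shifts are in units of that SD.
- *b* = 0; 4,000 simulated trials per row.

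| *c* | *a* | Mean change, *c* + *a*/2 | Paired t-test rejects | Between-condition test rejects |
|---|---|---|---|---|
| 0 | 0 | 0 | 5.6% | 4.6% |
| 0.2 | 0 | 0.2 | 58% | 4.8% |
| 0.3 | 0 | 0.3 | 91% | 4.8% |
| 0.5 | 0 | 0.5 | >99% | 4.9% |
| −0.25 | 0.5 | 0 | 3.9% | 77% |
| 0 | 0.5 | 0.25 | 76% | 77% |

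Normal-approximation checks:

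- Paired test at *c* = 0.2: 0.2 × √120 = 2.19, and Φ(2.19 − 1.96) = 0.59. At *c* = 0.3: 0.3 × √120 = 3.29, and Φ(3.29 − 1.96) = 0.91.
- Between-condition test at *a* = 0.5: 0.5 / √(2/60) = 2.74, and Φ(2.74 − 1.96) = 0.78.

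Rows 2 to 4 show the paired test rejecting when the modules do nothing. Row 5 shows it missing a real module effect. In row 6 the two tests agree, but only because *c* was set to zero, which the trial's data could not establish from the pre-post mean alone.

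**The case against.** The strongest defence is that the t-test was never offered as a test of the training. It stands in the closing paragraph, after the three research questions and next to the analysis of motivation after the support interviews. MAC2-A is introduced under the motivational support heading, to place participants in a stage of change at baseline. Table 1 keeps it apart from the secondary outcomes. No stated hypothesis concerns an effect of either module on it. A whole-sample description of motivation over the supported period fits all of that. The wording in Outcome measures is also loose, since MAC2-A sits in a list described as assessed at each measurement point and is then excepted from it.

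Much of this stands, and it limits the point. It does not remove it. Outcome measures does call MAC2-A a secondary outcome, and nothing in the document marks the t-test as descriptive. Nor is this a detail left to an unseen analysis plan: the article names a specific test for this measure.

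Three stronger readings are tempting and not supported:

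- *That the plan says it pools the arms.* It does not. A single test over all participants is the natural reading, but it is an inference. The point does not depend on it, because within-arm tests would also give no comparison.
- *That the randomised comparison is lost.* MAC2-A is collected before and after training in every arm, so the comparison remains available. Only the stated analysis leaves it unused.
- *That the plan attributes the change to the training or to the support.* It makes no such claim. The risk lies in how the result would be read.

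The usual precision gain from baseline adjustment is not a measure of the fault either. That gain is relative to an unadjusted comparison of post scores, which the plan does not propose.

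**Conclusion.** The point holds in a limited form. A measure listed as a secondary outcome is assigned a test that estimates neither module's effect nor the effect of motivational support, and the plan's condition-by-time model excludes it by its own wording. That follows from the text and from all arms sharing the support and usual care. It needs no numerical assumption.

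The rejection rates in the working only illustrate the direction of error. They rest on an assumed SD of change of 1, full recruitment and no loss. With the attrition that Sample size allows for, the power of the between-condition test would be lower than the 77% shown.

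The consequence is minor. It affects one secondary measure of mixed status in the document, with no stated hypothesis or power claim attached. The primary logistic regression on lapse or relapse is unaffected.

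**What to change.** Compare MAC2-A between the randomised conditions. Either of two models would do:

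- ANCOVA of the post-intervention score on baseline MAC2-A, with an indicator for each module and the stratification factors (gender and medication category, from the Randomisation section).
- The plan's own mixed ANOVA with two time levels and both module factors, reading the time-by-module terms.

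Report each module's difference with its 95% confidence interval. Keep the pre-post change as description only and say that it is not attributed to a cause. Bring Outcome measures and Table 1 into line on whether MAC2-A is a secondary outcome.

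The cost is a sentence or two of analysis wording. The measurements are already scheduled in all arms, so no new data, visits or participants are needed.
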